**Design**

As stated above the study is a randomized, controlled pilot study [1] with three arms:

1. TO with therapist support, choice between synchronous chat or asynchronous messaging, *n* = 20
2. TO with therapist support, asynchronous *messages,* n = 20
3. *TO without therapist support = 40*

Measurement based questionnaires (see below) occurs at recruitment to the study (T1) and at the completion of the study 10 weeks after recruitment (T2). See Figure 1 for the flow chart.

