TLFB (Timeline Follow Back) (Appendix 5.3) is an instrument for measuring the consumption of alcohol or drugs over time and has been used successfully in the periods up to 12 months back (Sobell & Sobell, 1992). There have also been attempts to use the method over a period of 24 months with mixed results (Day, Collins, Degenhardt, Thetford, & Maher, 2004). Sobell and Sobell (1992) generally suggest the help of a calendar chart during the time drinking should be assessed. Besides the calendar, you can use a written support to convert the amount of alcohol consumed to standard glass. Furthermore seeking man during the time period to identify so-called key dates (birthdays, holidays, weekends) and periods when drunk or abstention from alcohol. It then uses the key dates and periods as so-called anchor points to find out how much you drank then. One recommendation is to initially identify upper and lower limit for alcohol consumption during the period so that you know in which range you move. In the present study, we ask participants about their drinking during the last 7 days, as in the study conducted by Blankers et al. (2011). It is worth noting that no clear support existed for longer periods of study gives more reliable results.

RCQ (Readiness to Change Questionnaire) (Appendix 5.4) is a test developed to measure the motivation to change (Forsberg, Ekman, Halldin, & Rönnberg, 2004; Role Nick, Heather, Gold, & Hall, 1992). The test consists of 12 questions and follow DiClemente and Prochaska model of "stages of change" which describes the process when a person tries to solve its problems of dependence (Prochaska & DiClemente, 1986). In a recently published doctoral thesis psychiatric patients who changed their drinking habits after a short intervention from the beginning changed their habits to a greater extent than those who did not receive an intervention (Gordh, 2012). Questions have been raised about RCQs ability to predict outcomes (Forsberg et al., 2004).

VAS measures of motivation (Readiness Ruler) (Appendix 5. 4.1) consists of a scale where the respondent on a line places its response between two answers, in this case the statement *"I'm not ready to change my drinking habits" and "I'm very much ready to change my drinking habits."* High performance on the scale, especially in the upper tertiary, correlates with lower levels of drinking during follow-up after three months (Bertholet, Cheng Palfai, Samet, & Saitz 2009).

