**Procedure**

*Recruitment*

Recruitment for the study will be done through an ad posted on Alcohol Help [(www.alkoholhjalpen.se).](https://translate.google.com/translate?hl=sv&prev=_t&sl=sv&tl=en&u=http://www.alkoholhjalpen.se/) If recruitment in this way proves to be slow, ads on the Internet will be used. The advertisement informs that there is a study on the treatment of alcohol problems currently taking place and that there is the opportunity to participate. Those who show interest in participating must take part of the informed consent (see Appendix 4 .1) and specify gender and age, and fill in the AUDIT - form. If the inclusion criteria for age and / or hazardous use of alcohol is not met, the individual will be informed that the hazardous use of alcohol is not present in the answers, and that he / she therefore does not belong to the target group of the study (Annex 4.1. 1 .1). If the inclusion criteria are met, the participant receives information on this and creates a user account (Annex 4.1.1.2). Then the other questionnaires will be answered (see above under Materials). The randomization to the three study arms is fully automated. Participants may then immediately access the group via their own user account (Annex 4.1. 2-4). Participants will get access to a new module every week during the first 7 weeks. Then there is a break in treatment for three weeks. Then the participants get access to a finishing module. After completion of treatment, participants fill in outcome measurements again and processing issues and follow-up questions (Annexes 5.1-5.10).

*Treatment*

Participants in Group 1 who choose to have therapist support through chat, will receive this 40 minutes / week at a predetermined time. Chat for one will be in a private "chat room," on the treatment site they have access to through the personal user account. Participants in Group 1 who choose contact via messages, as well as participants in Group 2 will have access to therapist support through written messages once a week. The messages will be available through the treatment site. Participants will receive regular e-mail messages when messages from the therapist are posted on the treatment site. Participants in Group 3 will work on their own, without therapist support during treatment. These, however, if necessary, will be able to ask questions of the research team.

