**Statistics**

The results will be reported in anonymised form and statistical group level. Descriptive statistics for study participants' properties based on battery of questions will be presented, as well as analyses of the differences between the groups in the outcome. The primary measure of alcohol consumption is the AUDIT-C and TLFB. Secondary measures are other issues relating to anxiety, depression and quality of life. The analyses will be checked for motivation for treatment (Annex 5.4), other treatment during the study (treatment issues, Annex 5.10). Otherwise, additional results of the working alliance (Annex 5.8) and the platform's usability (Annex 5.9) will be presented.

This study is a pilot study in which the primary objective is to generate information and knowledge about various forms of Internet mediated therapist support. Since this is a pilot study we expect information about the feasibility and direction of outcomes (probably no significant differences). This is the first time that internet treatment with therapist support is tested in Sweden and the launch fits well with the National Board of Health guidance on disease prevention, where web-based treatment for problematic alcohol use is highlighted as an evidence-based action and which emphasizes that care must be equitable and accessible to all (National Board of Health, 2012).

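### The control variables named for the outcome analyses leave out the T1 value of AUDIT-C and TLFB, and no model is named that would bring it in

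*Protocol*

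**What the plan says.** The protocol's Statistics section plans analyses of group differences in outcome. It states "The primary measure of alcohol consumption is the AUDIT-C and TLFB". It then says "The analyses will be checked for motivation for treatment (Annex 5.4" and goes on to "other treatment during the study (treatment issues, Annex 5.10". The text appears to be a machine translation, and 'checked for' is best read as 'controlled for': in the Materials section, the description of the Annex 5.10 form gives controlling for other factors as its purpose.

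The Design section says that measurement "occurs at recruitment to the study (T1) and at the completion of the study 10 weeks after recruitment (T2". The Procedure section gives the order at entry. Candidates "specify gender and age, and fill in the AUDIT - form", which contains the three AUDIT-C items. After the account is created, "Then the other questionnaires will be answered (see above under Materials". Automated randomisation is described next. The outcome measures are filled in again after treatment.

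No section names the T1 value of AUDIT-C or TLFB as a control variable. None says whether the analysed quantity is the T2 value, the change from T1, or both time points in a repeated-measures model.

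**The concern.** Once a protocol says what the outcome analyses are controlled for, one looks first for the baseline value of the outcome, which is usually a strong predictor of the follow-up value. It is not there.

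Two things are at stake. The first is precision: the main comparison is 40 v 40 (groups 1 and 2 against group 3), and the comparison of the two supported arms is 20 v 20. The second is chance imbalance. No stratification is described, so the T1 means of the arms can differ by chance, and without adjustment part of that difference passes into the outcome contrast. The pilot wants to learn the direction of outcomes, and a baseline gap can distort a direction.

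**Working it through.** **Inputs from the protocol.** Total 80; arms 20, 20 and 40; groups 1 and 2 together (40) against group 3 (40); measurement at T1 and T2. The protocol gives no SD, effect size, alpha, power or dropout rate, so there is no figure to reproduce.

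**Assumptions.** T1-T2 correlation r = 0.3, 0.5 or 0.7; equal variance at T1 and T2; no dropout; 95% intervals. If motivation also stays in the model, r should be read as the correlation left after allowing for it.

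**Step 1: variance factors**, with a T2-only comparison set to 1. The change score has factor 2 − 2r and adjustment for T1 has factor 1 − r². The equivalent number of participants is 80/(1 − r²), before the small-sample penalty in Step 3.

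| r | T2 only | Change score | T1-adjusted | Equivalent N |
|---|---|---|---|---|
| 0.3 | 1 | 1.4 | 0.91 | 87.9 |
| 0.5 | 1 | 1.0 | 0.75 | 106.7 |
| 0.7 | 1 | 0.60 | 0.51 | 156.9 |

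**Step 2: can a change score replace adjustment?** (2 − 2r) − (1 − r²) = (1 − r)², which is positive for every r below 1. The change score is therefore always less precise. Relative to it, adjustment lowers the variance by 1 − 0.91/1.4 = 35%, 1 − 0.75/1.0 = 25% and 1 − 0.51/0.60 = 15%. An unconstrained group-by-time model with two time points and complete data gives the same contrast as the change score. A model that constrains the arms to a common T1 mean does not lose this precision.

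**Step 3: interval half-widths in SD units.** The unadjusted SE is √(1/n₁ + 1/n₂): √(1/40 + 1/40) = 0.224 and √(1/20 + 1/20) = 0.316. The adjusted SE multiplies this by √(1 − r²) and by the small-sample penalty √(1 + 1/(n₁ + n₂ − 4)), with one degree of freedom fewer in the t quantile. Example, 40 v 40, r = 0.5: 0.2236 × √0.75 × √(1 + 1/76) = 0.195, half-width 0.388.

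| Contrast | r | T2 only | Change score | T1-adjusted |
|---|---|---|---|---|
| 40 v 40 | 0.3 | 0.445 | 0.527 | 0.428 |
| 40 v 40 | 0.5 | 0.445 | 0.445 | 0.388 |
| 40 v 40 | 0.7 | 0.445 | 0.345 | 0.320 |
| 20 v 20 | 0.3 | 0.640 | 0.757 | 0.620 |
| 20 v 20 | 0.5 | 0.640 | 0.640 | 0.563 |
| 20 v 20 | 0.7 | 0.640 | 0.496 | 0.464 |

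**Step 4: price if T1 predicts nothing (r = 0).** The half-width rises from 0.445 to 0.448 (40 v 40) and from 0.640 to 0.650 (20 v 20).

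**Step 5: chance imbalance.** For 20 v 20 the T1 difference has SD 0.316, so a gap above 0.3 SD has z = 0.3/0.316 = 0.95 and occurs about one time in three. A T2-only contrast takes in r times the gap: at r = 0.5, 0.5 × 0.3 = 0.15 SD.

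**The case against.** The strongest objection is that model and covariates are ordinary SAP content, and an SAP may exist. The protocol names no model and does not call its list complete. Measurement at both T1 and T2 fits a pre-post analysis as well as a T2-only one. This largely stands: it makes the loss conditional. It does not remove the point, because the protocol did choose to state control variables and left out the most obvious one. A change-score reading would not repair that (Step 2).

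A reader might infer that the pilot does discard T1 and so loses the equivalent of 27 to 77 participants (107 − 80 and 157 − 80). The documents do not support this. No T2-only analysis is stated, and r is not given. A low r is plausible: entry requires a minimum AUDIT score, TLFB covers only 7 days, and treatment falls between the two measurements. At r = 0.3 the gain over a T2-only comparison is 9% of variance.

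A reader might also infer that the plan kept a weak covariate in place of a strong one, since the Materials section says "Questions have been raised about RCQs ability to predict outcomes". That is selective. The same section reports that high scores on the Readiness Ruler, also a motivation measure under Annex 5.4, correlate with lower drinking at three months. The RCQ's merits also have no bearing on whether T1 drinking is used.

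Finally, the pilot seeks feasibility and direction, expects probably no significant differences and makes no power claim. This stands and limits the severity. Nor is information for the later powered trial lost: T1 and T2 are both collected, so their correlation can be estimated whichever covariates the pilot uses.

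**Conclusion.** The point holds conditionally. The stated control variables omit the T1 value of both primary measures, that value is available before randomisation, and no model is named that would bring it in. If T1 is not used through a baseline-adjusted or constrained model, the avoidable variance is 9% to 49% of that of a T2-only comparison, or 15% to 35% of that of a change score, for assumed r between 0.3 and 0.7. These figures assume equal variances and complete data. The improvement is worth making but its consequence is moderate, since no stated power or precision target is missed.

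**What to change.** Add one sentence to the Statistics section: each T2 outcome is compared between the randomised groups by ANCOVA with the T1 value of the same outcome as covariate, or by an equivalent mixed model with the T1 means constrained equal across arms. T1 motivation may stay as a second covariate. If an SAP exists, it should say the same.

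The cost is one sentence and one degree of freedom, with no new data. Other treatment during the study is a separate matter: it arises after randomisation and may be affected by arm, so adjusting for it can bias the comparison. Adding T1 does not settle whether it should stay.
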